#### Primary outcome: success of the intervention

The response to the intervention will be evaluated using performance in the Corsi test [25]: an increase of at least 1 point will indicate a success based on the enhancement of the spatial learning processes.

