### Randomisation

The selected subjects will be randomly allocated to the experimental group (EG, *n* = 150) or to the control group (CG, *n* = 150) using a randomisation list.

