### Sample size calculation

It was based on the null hypothesis that proportion of “success” and “failure” of the intervention is equal in the two groups (i.e., EG and CG), such as OR = 1.

Success and failure were defined on the basis of significant variation in the primary outcomes. Considering an OR = 1.5 indicative of an effect of the intervention, a total sample of 300 subjects allows us to reach a 90% of statistical power using logistic regression at the 5% level (two tailed). Drop-out rate was set at 20%.

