### Statistical analysis

All data will be collected in a database. A descriptive analysis will be performed to assess the distribution of variables and the presence of possible outliers. The latter will be checked and identified separately and then excluded from the analysis. For normally distributed variables, the comparisons between EG and CG at baseline will be carried out by *t *Student test or Chi-square test, while those between baseline and follow-up phases by paired sample *t* test. For non-normally distributed variables, non-parametric tests will be used. Correlation analysis will be performed to evaluate the relationships among variables and general linear models and repeated measures ANOVA will be used to assess the intervention effects adjusted for confounding variables (e.g., gender, age classes, marital status, schooling, drugs, and other variables that will emerge after analysis of secondary outcomes). The SPSS software will be employed.

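### The plan sizes and defines its primary outcome as a 1-point Corsi responder but names linear models for effects, with baseline Corsi unnamed; one baseline-adjusted analysis of the score should be fixed as primary

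*Protocol article*

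**What the plan says.** Three sections of the Protocol article bear on the primary analysis.

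- **Primary outcome: success of the intervention** turns the Corsi result into a responder status: "an increase of at least 1 point will indicate a success based on the enhancement of the spatial learning processes".
- **Sample size calculation** works on the same dichotomy, with an odds ratio of 1.5 as the effect to detect. It states that "a total sample of 300 subjects allows us to reach a 90% of statistical power". The test named there is a two-sided logistic regression at 5%, and drop-out is put at 20%.
- **Statistical analysis** does not mention logistic regression. It says that "general linear models and repeated measures ANOVA will be used to assess the intervention effects". The covariates are given as an open list of five examples (sex, age group, marital status, education and drugs), to be extended by variables that emerge later from the secondary outcomes. Baseline Corsi is not named.

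The Abstract says that all outcomes are assessed at baseline and at three follow-ups, so the baseline score will be in hand.

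**The concern.** A cut at 1 point treats a rise that just meets the threshold and a much larger rise as the same result. It also treats no change and a clear decline as the same result. The second matters in a trial that aims to counteract cognitive decline. A response defined by change also depends on where the participant started, because scores that are low by chance tend to rise on retest. Baseline Corsi is therefore an obvious covariate, and the plan does not name it.

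The models in the analysis section suit a quantitative score, whereas the outcome definition and the sizing suit a success proportion. The same data could thus give two primary results of quite different precision, and the plan does not say which one counts.

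**Working it through.** **Inputs from the Protocol article:** OR 1.5, two-sided 5%, 300 subjects at 1:1 (150 per arm), 20% drop-out. If the 300 are counted before drop-out, 240 complete (120 per arm).

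**Inputs assumed, because the document gives none:** control success rate 20–50%; approximately normal change in Corsi; baseline/follow-up correlation ρ of 0.5–0.8; independent participants.

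**Step 1. The plan's own figure.** A two-arm comparison of proportions at OR 1.5 with 300 analysed has at most 41.6% power (control rate 45%), and at most 34.6% with 240. The stated 90% is not reproduced. The formula for a continuous predictor, N = (z_α + z_β)² / [p(1−p)(ln OR)²], comes close, with 89.6% at p = 0.30, but it does not fit a two-group factor. This sizing problem is separate from the present point. It matters here because a trial this short of power has little information to spare.

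**Step 2. The cut against the change score.** Relative efficiency = φ(z_p)² / [p(1−p)].

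- p = 0.50: 0.3989² / 0.25 = 0.64, a loss of 36%
- p = 0.30: 0.3477² / 0.21 = 0.58, a loss of 42%
- p = 0.20: 0.2800² / 0.16 = 0.49, a loss of 51%

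**Step 3. The change score against ANCOVA.** The change has variance 2σ²(1−ρ). The baseline-adjusted score has residual variance σ²(1−ρ²). The ratio of the second to the first is (1+ρ)/2, which is 0.75 at ρ = 0.5, 0.85 at 0.7 and 0.90 at 0.8. Baseline adjustment thus removes 25% down to 10% of the variance. This is also the gain over repeated measures ANOVA with two time points, where the group-by-time test is a test of change.

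**Step 4. The unadjusted cut against ANCOVA** (product of steps 2 and 3).

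| Success rate | ρ = 0.5 | ρ = 0.7 | ρ = 0.8 |
|---|---|---|---|
| 0.50 | 0.48 | 0.54 | 0.57 |
| 0.30 | 0.43 | 0.49 | 0.52 |
| 0.20 | 0.37 | 0.42 | 0.44 |

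For success rates of 30–50% the loss is 43–57%, and it reaches 63% in the 20% row. Put another way, 240 completers analysed by the cut carry the information of about 240 × 0.43 = 104 to 240 × 0.57 = 138 analysed by ANCOVA.

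**Step 5. Power at the effect that matches OR 1.5.** A control rate of 40% gives odds 0.667 × 1.5 = 1.0, so the success rate in the experimental group is 50%. The matching shift is Φ⁻¹(0.50) − Φ⁻¹(0.40) = 0.253 SD of change.

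| Analysis | 300 analysed | 240 analysed |
|---|---|---|
| Responder, unadjusted | 41% | 34% |
| Change score | 59% | 50% |
| ANCOVA, ρ = 0.5 | 72% | 62% |
| ANCOVA, ρ = 0.7 | 66% | 57% |
| ANCOVA, ρ = 0.8 | 64% | 54% |

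**Step 6. Simulation check** (120 per arm, 1,500 replicates, control success rates of about 30% and 40%, ρ 0.5–0.8). The unadjusted cut lost 44–55% against ANCOVA with continuous scores and 37–55% with integer scores. Logistic regression with baseline added still lost about 30–48%, so most of the loss comes from the cut itself.

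**The case against.** The strongest objection is that the analysis section names methods for a quantitative outcome, while logistic regression appears only in the sizing text. If those methods are applied to the Corsi score, the loss from the cut never arises and only the 10–25% from baseline adjustment remains. This stands, and it limits the claim. A reader might infer that the trial certainly gives up a third to a half of its information, but the document does not say that the cut is what will be tested.

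A reader might also infer that baseline Corsi has been excluded from the model. It has not: the list begins with e.g. and stays open, and a journal article may leave the final list to a fuller document. It is simply unnamed. The grouping of age into classes might look like a further loss, but it is a matter of coding, no size can be put on it from this document, and it is no part of this point. Nor does unadjusted baseline imbalance bias a randomised comparison; it costs precision.

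A responder threshold is a recognised choice made for ease of interpretation, and it can be kept. What survives the objection is that the sizing and the outcome definition both point to a responder comparison, the analysis section points elsewhere, and the efficient option uses data already collected.

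**Conclusion.** The point holds conditionally. The outcome definition and sample size section are not aligned with the analysis section, and which of them governs decides how much is lost: about 43–57% against ANCOVA if the unadjusted cut is tested (36–51% against the change score), or 10–25% if change is tested. These figures rest on assumed success rates, correlation and normality. They are a range, not a property of the trial.

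It would be wrong to conclude that ANCOVA rescues the power claim. At the effect matching OR 1.5, with a 40% control rate, it reaches about 54–72%, not 90%. Those powers also assume independent participants, although the intervention is taught in classes of about 25.

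**What to change.** State one primary analysis and make the outcome, sample size and analysis sections agree on it. The preferred choice is the between-arm difference in Corsi score at follow-up 1, from a linear model with baseline Corsi as a continuous covariate, with the proportion gaining at least 1 point reported beside it. If the responder outcome stays primary, name logistic regression in the analysis section and put baseline Corsi in that model.

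No new data or visits are needed, but this is more than a change of wording:

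- It changes the primary outcome of a trial that began on 1 August 2019, so it should be a documented amendment made before any comparison by arm.
- The OR-based sizing statement must be restated for a mean difference, with its assumed SD and correlation.
- The headline becomes a mean difference in points, which is less immediate to readers than a success rate.
- A score-based primary comes directly under the plan's rule that outliers are removed from analysis, so the amendment should say how that rule applies to the Corsi score.

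Adding baseline Corsi to whichever model is kept costs almost nothing.

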#### Secondary outcomes

They include:the assessment of the intervention effects on lifestyle characteristics as well as psychological, functional and health status;the assessment of the intervention effects on mobility;the investigation of the conversion rate from MCI to dementia;the identification of biomarkers able to mirror the intervention effects.

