**Fig. 1 Fig1:**
[figure not shown]
Flowchart of strength project

#### Specific aim 1

To study the effect of the multimodal intervention on cognitive performances, functional status, and mobility in MCI subjects by objectively measured parameters (baseline vs. follow-up 1, follow-up 2 and follow-up 3). Mobility (i.e., the ability of a subject to move in his/her environment) is often compromised in elderly people as a consequence of falls and other injuries and this could cause disability and reduced social engagement. The identification of approaches that might prevent motor–cognitive impairment would be a pivotal advancement in the correct management of aging people. Mobility will be evaluated by means of balance, walking test and gait speed; motor–cognitive function, defined as a process of coordination of movements finalized to a particular motor goal, will be measured by means of visual–spatial memory task.

The longitudinal monitoring of cognitive decline and dementia onset will also be implemented (follow-up 2 and follow-up 3).

#### Specific aim 2

To study the effect of the intervention on psycho-social aspects (e.g., psychological well-being, perceived stress, quality of life, metacognition and mood status), lifestyle characteristics and social network (baseline vs. follow-up 1, follow-up 2 and follow-up 3).

#### Specific aim 3

To study the effect of the intervention on specific biomarkers (baseline vs. follow-up 1, follow-up 2 and follow-up 3).

#### Experimental design aim 1

Neuropsychological as well as cognitive and clinical assessment, including cardiovascular, anthropometric, and functional evaluation (e.g., blood pressure, body mass index, ultrasound heart examination through standard echocardiogram, 6-min walk test, gait speed, Berg Balance Scale, handgrip strength, Physical Activity Scale for the Elderly, basic activities of daily living and instrumental activities of daily living) will be carried out (Table 1).

**Table 1 Tab1:** Clinical, functional, and neuropsychological assessment

Instruments
*Cognitive assessment*
Clinical Dementia Rating Scale—CDR [20]
Memory Complaint Questionnaire—MAC-Q [21]
Montreal cognitive assessment—MoCA [22]
Mini mental state examination—MMSE [23]
Rey auditory verbal learning test—RAVLT [24]
Phonological verbal fluency—PVF [24]
Supra-span of Corsi [25]
Semantic verbal fluency—SVF [26]
Attentive matrices [26]
Trail making test A−B—TMT A–B [27]
*Psychological assessment*

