Depression Anxiety Stress Scale—DASS [28, 29]
Geriatric Depression Scale-15—GDS-15 [30]
Psychological Well-Being Scales—PWB [31, 32]
SF-36 (36 health survey) [33]
*Functional assessment*
Basic activities of daily living—ADL [34]
Instrumental activities of daily living—IADL [35]
Berg Balance Scale—BBS [36]
6-min walking test—6MWT [37]
*Social network*
Lubben Social Network Scale—LSNS [38]
*Lifestyle characteristics and physical activity*
Physical Activity Scale for the Elderly—PASE [39]
Lifestyle Questionnaire

#### Experimental design aim 2

Enrolled subjects will undergo a detailed protocol of tests and questionnaires to evaluate the following aspects: psychological well-being, perceived stress, quality of life, metacognition, mood status, lifestyle characteristics and social network (Table 1) [20–39].

#### Experimental design aim 3

The following parameters will be evaluated (details are reported in Fig. 2):BDNF and ceruloplasmin protein amounts in plasma and their mRNA expression in peripheral blood monuclear cells (PBMC), as the role of peripheral leukocyte dysfunctions in Alzheimer’s disease (AD) development [40, 41] is well known;mRNA expression in PBMC of 84 key genes involved in AD physiopathology (i.e., beta-amyloid generation, oligomerization, clearance, and degradation; cytoskeleton regulators; synaptic formation; lipid metabolism; apoptosis; cell cycle; cell signalling molecules; transcriptional regulation; oxidative stress; proteases and protease inhibitors);plasma copper, zinc, and other important micronutrients;a panel of the most common laboratory parameters.

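### The intervention-effect models may be adjusted for variables that emerge from the secondary-outcome analyses, so post-randomisation markers chosen from the data can enter as confounders

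*Protocol article*

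**What the plan says.** All references are to the Methods of the protocol article.

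- **Statistical analysis.** General linear models and repeated-measures ANOVA assess the intervention effects with adjustment for confounders. The examples are gender, age class, marital status, schooling and drugs, "and other variables that will emerge after analysis of secondary outcomes".
- **Secondary outcomes.** Four groups are listed: lifestyle, psychological, functional and health status; mobility; conversion to dementia; and "the identification of biomarkers able to mirror the intervention effects".
- **Specific aim 3.** The purpose is given as "To study the effect of the intervention on specific biomarkers (baseline vs. follow-up 1, follow-up 2 and follow-up 3".
- **Experimental design aim 3.** The candidates are "BDNF and ceruloplasmin protein amounts in plasma and their mRNA expression" in blood cells, "mRNA expression in PBMC of 84 key genes involved in AD physiopathology", "plasma copper, zinc, and other important micronutrients", and "a panel of the most common laboratory parameters".
- **Sample size calculation.** The only significance level in the article is here, for the primary outcome: "using logistic regression at the 5% level (two tailed". None is given for biomarkers, and a multiplicity correction is neither prescribed nor excluded.

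**The concern.** In a randomised comparison, the variables worth adjusting for are those fixed before allocation. A variable measured afterwards that differs between the arms does so by chance, through selective drop-out, or because the intervention changed it. In the last case it is a result of treatment, and conditioning on it changes the question being answered.

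The covariate list is left open, and the analyses that may add to it are those of the secondary outcomes. These are largely follow-up measurements that the trial expects the intervention to move. The better a biomarker meets the stated goal of mirroring the intervention, the more damage it does as a covariate. The same applies to mobility, mood or social activity used to adjust a cognitive outcome. At stake are the adjusted estimates of the intervention effect, which this sentence covers without separating one outcome from another.

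**Working it through.** The plan gives no figure on this point to reproduce, so the check sets the sections side by side and then sizes the consequence.

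**Step 1. What the rule admits.** The covariate sentence points to the analysis of secondary outcomes. The Secondary outcomes section includes biomarker identification, and Specific aim 3 places the measurements at baseline and three follow-ups. Analysis of those outcomes can only follow collection of post-randomisation data. Nothing in the sentence limits the added variables to baseline values. Selected biomarkers, as follow-up values or changes, are therefore within its scope, although it does not name them.

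**Step 2. A marker that truly responds.** Put outcome Y and marker M in within-arm SD units. Let D_Y and D_M be their between-arm differences at follow-up, and r their within-arm correlation. In a linear model with arm and M:

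adjusted difference = D_Y − r × D_M

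The documents give neither r nor D_M. Assumed values:

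| D_M | r = 0.3 | r = 0.5 |
|---|---|---|
| 0.3 | 0.09 | 0.15 |
| 0.4 | 0.12 | 0.20 |
| 0.5 | 0.15 | 0.25 |

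The entries are the amounts r × D_M by which the estimate moves, in SD of Y. If D_Y is also 0.4 and D_M = 0.4, the adjusted difference is 0.4 − 0.12 = 0.28 or 0.4 − 0.20 = 0.20, a loss of 30% or 50%. If r and D_M have opposite signs, a positive D_Y is inflated instead. If r = 0, nothing changes.

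**Step 3. A marker picked up by chance.** Evaluable per arm: 150 × (1 − 0.20) = 120. Suppose, as an assumption, that variables emerge by crossing a two-sided 5% threshold between arms. An unaffected marker that does so differs by at least 1.96 × √(2/120) = 1.96 × 0.129 = 0.253 SD. Entering it moves the estimate by at least r × 0.253, which is 0.076 SD at r = 0.3 and 0.127 SD at r = 0.5. The standard error of the unadjusted outcome difference is itself about 0.129 SD. The model, and so the estimate, depends on which markers happened to cross.

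**Step 4. Size of the candidate pool.** There are 84 genes, 4 measures of BDNF and ceruloplasmin (protein and mRNA), 8 micronutrients and at least 11 laboratory parameters in the Fig. 2 legend: 84 + 4 + 8 + 11 = 107 or more. If every one of the 84 genes were null and each were tested at 5%, the expected false hits per comparison would be 84 × 0.05 = 4.2, whatever their correlation. The chance of at least one would be 1 − 0.95^84 = 98.7% under independence. These figures are conditional: the article states no test level for the genes.

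**The case against.** The case on the other side has three parts.

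1. **The named confounders are mainly subject characteristics, so the open tail may mean more of the same.** That reading is possible, but the text does not say so. Even on that reading the covariates would be chosen after outcome data had been analysed.
2. **The sentence mentions neither biomarkers, nor genes, nor selection by significance.** This stands. The rule permits selected biomarkers as covariates; it does not prescribe them.
3. **The article condenses a full protocol and an analysis plan that are not shown.** This stands for multiplicity handling of a secondary panel, which is commonly left to such documents. It does not remove the covariate sentence, which is written here. A multiplicity rule elsewhere would reduce chance hits (Step 3) but would leave a truly responding marker in the model (Step 2).

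A reader might also infer that the plan prescribes unadjusted 5% tests, giving 12.6 false genes over three follow-ups (252 × 0.05) and a biomarker list that is largely false. The documents do not support this.

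- The 5% level belongs to the primary sample size. The methods named for the effect analysis can be used with or without a correction.
- Repeated-measures ANOVA can give one group-by-time test per gene, hence 84 tests rather than 252.
- The false share among hits is (1 − p) × 0.05 / [(1 − p) × 0.05 + p × power], with p the share of markers truly affected. At p = 0.10 it is 0.045/(0.045 + 0.09) = 33% with 90% power and 0.045/(0.045 + 0.03) = 60% with 30% power. At p = 0.50 it is 0.025/(0.025 + 0.45) = 5% and 0.025/(0.025 + 0.15) = 14%. The article gives neither p nor the power per marker.

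**Conclusion.** The point holds for the covariate rule. As written, it lets data-selected, post-randomisation variables, including biomarkers identified as responding to treatment, be used as confounders in the models that estimate the treatment effect. That can remove or distort part of the effect, and it makes the estimate depend on the selection. The size is r × D_M: 0.09 to 0.25 SD over the ranges shown. It rests on assumed correlations and shifts, on a linear model, and on the rule being applied to follow-up or change values.

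The absence of stated error control for the biomarker search is not shown to be an error. It supports a recommendation only, with 4.2 expected false hits per comparison as a conditional illustration.

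**What to change.** **Change.** In the Statistical analysis section, delete the phrase that lets covariates emerge from the secondary analyses. Restrict adjustment of the intervention-effect models to a pre-specified list of baseline covariates: those already named, as recorded before allocation, plus the baseline value of the outcome analysed. State that follow-up or change values of biomarkers or other secondary outcomes will not be covariates in those models.

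**Cost.** One sentence is reworded, with no new data or subjects. The only loss is the freedom to add covariates later.

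**Recommendation, separate from the change.** Report the 84-gene panel with false discovery rate control, or label the biomarker identification exploratory. With error control, fewer genes would be declared. Which test and which families of markers to use are design choices for the sponsor.

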### Statistical analysis

All data will be collected in a database. A descriptive analysis will be performed to assess the distribution of variables and the presence of possible outliers. The latter will be checked and identified separately and then excluded from the analysis. For normally distributed variables, the comparisons between EG and CG at baseline will be carried out by *t *Student test or Chi-square test, while those between baseline and follow-up phases by paired sample *t* test. For non-normally distributed variables, non-parametric tests will be used. Correlation analysis will be performed to evaluate the relationships among variables and general linear models and repeated measures ANOVA will be used to assess the intervention effects adjusted for confounding variables (e.g., gender, age classes, marital status, schooling, drugs, and other variables that will emerge after analysis of secondary outcomes). The SPSS software will be employed.

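### Outliers found after data collection are to be dropped without limiting this to verified errors, which can bias the between-arm comparison, mainly for the continuous secondary outcomes

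*Protocol article*

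**What the plan says.** All of the relevant text is in the Statistical analysis section of the protocol article.

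- **Screening:** "A descriptive analysis will be performed to assess the distribution of variables and the presence of possible outliers". This covers variables in general and is not confined to baseline.
- **Action:** "The latter will be checked and identified separately and then excluded from the analysis".
- **Effect analysis:** "general linear models and repeated measures ANOVA will be used to assess the intervention effects adjusted for confounding variables".
- **Skewed data:** "For non-normally distributed variables, non-parametric tests will be used".

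The primary outcome, defined in its own section, is a Corsi test success: "an increase of at least 1 point will indicate a success based on the enhancement of the spatial learning processes". The secondary outcomes include lifestyle, psychological, functional and mobility measures, biomarkers, and conversion to dementia.

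The article does not limit the exclusion to recording errors, does not require blinding to arm, and plans no analysis with the excluded values kept.

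**The concern.** A follow-up value is measured after randomisation and may be affected by the intervention. If such values are removed because they are extreme, who stays in the analysis depends on the outcome, and the retained groups are no longer those that were randomised. In this trial an extreme change may be exactly what is being studied: a marked gain after the programme or a sharp decline.

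The planned effect models compare means, so they respond directly to which tail is cut. Exclusion is not needed to cope with extremes, because the plan already has non-parametric tests for non-normal variables.

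This is not a detail left for a later document. The article states the action, which is exclusion. A numerical cut-off in an SAP would make the rule reproducible, but genuine values would still be dropped.

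**Working it through.** The plan gives no figure for the effect of this rule, so there is none to reproduce. The check asks how much of a known effect survives exclusion.

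**Inputs**

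- 150 per arm (Randomisation) and 20% drop-out (Sample size calculation): 150 × 0.80 = 120 per arm, taking drop-out to come off the 150.
- Cut-off: not stated. Three common rules are tried, each applied to both arms pooled: mean ± 2 SD, mean ± 3 SD, and 1.5 × IQR fences.
- Response pattern: not stated. Assumed: controls N(0,1) and a true difference of 0.30 SD, arising either as (A) a uniform shift of 0.30 SD in the experimental arm, or (B) 10% of that arm gaining 3 SD and the rest nothing (0.10 × 3 = 0.30).

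**Large-sample calculation, 2 SD rule, pattern B**

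1. Pooled mean = 0.05 × 3 = 0.15. Pooled variance = 1 + 0.05 × 9 − 0.15² = 1.4275, so SD = 1.195.
2. Limits = 0.15 ± 2 × 1.195, that is −2.24 to 2.54.
3. Excluded among strong responders: P(Z > 2.54 − 3) = 0.677. Excluded among everyone else: P(Z > 2.54) + P(Z < −2.24) = 0.0055 + 0.0125 = 0.018.
4. Excluded by arm: experimental 0.10 × 0.677 + 0.90 × 0.018 = 8.4%; control 1.8%.
5. With limits a and b, a component N(m,1) contributes m[Φ(b−m) − Φ(a−m)] + φ(a−m) − φ(b−m) to the retained total. Weighting by component and dividing by the retained share gives means of 0.083 (experimental) and 0.017 (control).
6. Remaining difference = 0.083 − 0.017 = 0.066. Loss = 1 − 0.066/0.30 = 78%.

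**Same rule, pattern A.** Pooled variance = 1 + 0.15² = 1.0225, SD = 1.011, limits −1.87 to 2.17. Each arm loses 4.55%, the remaining difference is 0.234, and the loss is 22%.

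**Simulation, 120 per arm** (loss = 1 − remaining/0.30; exclusions are mean numbers of participants, experimental v control)

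| Rule | A: remaining (loss) | A: excluded | B: remaining (loss) | B: excluded |
|---|---|---|---|---|
| 2 SD | 0.236 (21%) | 5.4 v 5.4 | 0.07 (77%) | 10.0 v 2.2 |
| 1.5 × IQR | 0.283 (6%) | 1.0 v 1.0 | 0.11 (63%) | 6.8 v 0.6 |
| 3 SD | 0.293 (2%) | 0.3 v 0.3 | 0.21 (30%) | 2.7 v 0.0 |

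Under pattern B with 150 per arm, power falls from about 58% to 9% (2 SD), 17% (IQR) and 36% (3 SD).

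**No true effect.** With the same fixed pooled rules, the mean difference stays at zero and the rejection rate is 5.0–5.3%.

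**Binary outcome.** A gain just over the threshold and a very large gain both count as one success, so an extreme value carries no extra weight. Two illustrations:

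- Success taken as a change of at least 0.5 SD (assumed). Under pattern A the odds ratio is 1.62 without exclusion and 1.56–1.63 with it. Under pattern B it falls from 1.36 to 1.12–1.27.
- An unfavourable case: 5% of the experimental arm (7.5 of 150) is excluded and all are successes, starting from the plan's OR of 1.5. At an assumed control rate of 0.40, experimental successes are 75 of 150. After exclusion the odds are 67.5/75 = 0.90, and OR = 0.90/(0.40/0.60) = 1.35. At a control rate of 0.30 the same step gives 1.31.

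**The case against.** The strongest reply is that the rule is read too harshly and its harm overstated. The sentence names a checking step, it comes from a condensed article, and it spans many variables, including laboratory assays and an 84-gene expression panel, where screening out measurement artefacts is a sensible purpose. It does not say whether a value or a whole participant is removed. The cut-off and blinding may be set in an SAP.

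Part of this stands. Four stronger conclusions that a reader might draw are not supported:

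- **That bias is certain.** It is conditional. Under a uniform shift with a 3 SD or IQR rule, the loss is 2–6% and exclusions are balanced.
- **That most of a real effect would be lost.** That needs a strongly responding subgroup, and nothing in the article indicates one.
- **That trimming gives falsely small standard errors and hence false positives, or moves the estimate in either direction.** With a fixed pooled rule the type I error stays near 5%, and every non-null case for the continuous mean difference shows attenuation. Inflation would need a cut-off set by arm or chosen with allocation known, which the article does not state.
- **That the primary outcome is badly compromised.** It is binary, so extremes have little leverage. Likewise, screening a continuous variable does not by itself remove participants from the count of dementia conversions.

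The checking step does not rescue the rule. The sentence ends in exclusion, and nothing says that a value confirmed as genuine is kept.

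**Conclusion.** The rule is badly fixed and should be changed. As written, it allows genuine follow-up values of randomised participants to be dropped because of their size, which can bias the comparison of arms. The main exposure is in the continuous secondary outcomes. The Corsi primary outcome is less affected, although a participant removed as an outlier is lost from the randomised arm and the odds ratio can then move.

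For an assumed 0.30 SD difference with 120 per arm, the loss is about 2–21% under a uniform shift and about 30–78% if 10% of the experimental arm gain 3 SD. These ranges illustrate and do not predict: they rest on normal data, a pooled rule fixed in advance, and cut-offs and response patterns that the article does not give. Under the null such a rule causes neither bias nor type I error inflation.

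**What to change.** Replace the exclusion sentence with wording such as:

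> Outliers will be queried against source, blind to allocation. Only verified errors will be corrected or set to missing. All other values of randomised participants stay in the primary analysis, and a rank-based or robust analysis will show sensitivity to extreme values.

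Settle this before outcome data are examined by arm. It costs one sentence and one added sensitivity analysis, and error bars will be somewhat wider where extreme values are genuine. Screening of assay artefacts can continue, because a verified measurement error may still be corrected or set to missing.
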